### Design and Outcomes

We will conduct a multi-site cluster randomized trial of 3 behavioral interventions targeting unnecessary antibiotic prescribing during ambulatory visits for acute respiratory infections (ARIs), with practice as the unit of randomization.

The main outcome will be the rate of antibiotic prescribing for ambulatory visits for acute respiratory infections in which antibiotics are inappropriate (i.e., prescribing an antibiotic is inconsistent with published guidelines).

In the main analysis, we will compare a 6-month baseline period to an 18-month intervention period. In subsequent secondary analysis, we will track antibiotic prescribing for another 12 months after the interventions end.

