## **9. STATISTICAL CONSIDERATIONS**

### **9.1 General Design Issues**

#### *Hypotheses*

Our primary hypothesis is that practices randomized to receive behavioral economic interventions will have decreases over time in antibiotic prescribing rates for non-antibiotic appropriate ARIs, compared to contemporaneous antibiotic prescribing rates for non-antibiotic appropriate ARIs among control practices. This hypothesis will be evaluated in an intent-to-treat difference-in-differences framework using a mixed-effects logistic regression model. Fixed effects will include the effects of interventions over time (i.e., interactions between randomization assignment and time), using a 6-months prior to the intervention baseline period. Providers and randomization unit (clinic) will be modeled as random effects.

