## 9.2 Sample Size and Randomization

Using the correction for inter-cluster correlation from Kish, we estimated the power of our study to detect a clinically significant difference between binary conditions. That is, the sample size must be inflated by a factor of  $1 + \theta(m-1)$ , where  $\theta$  is the inter class correlation and  $m$  is the number of ARI observations per cluster. In our calculations we assumed an intra-clinic correlation of 0.05 and assumed a baseline antibiotic prescribing rate of 50%, an ARI visit rate of 15 visits per month for full time providers, and independence of treatments in the factorial design. We calculated the number of visits needed for an 80% chance (1 – Type II error) to detect a clinically meaningful difference in antibiotic prescribing (7%). We assumed Type I alpha is equal to 0.05, a 75% recruitment success rate for recruiting 376 eligible providers across 49 sites, resulting in 141 providers per study factor (282 clinicians total) and a one-sided  $\alpha$  of 0.05. To achieve statistical power of 0.80 would require a total of 2,252 visits at each factor level, or 4,504 visits across all study conditions. Therefore, if each provider had a minimum of 16 antibiotic-inappropriate ARI visits over the course of the study, we would have sufficient power to detect a clinically significant effect. Randomization is described next in Section 9.2.1.

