### 9.5 Data Analyses

We will use the following descriptive statistics to characterize the sample: Means and medians for continuous measures, frequencies for count data, standard deviations and interquartile ranges for variance.

For inferential analysis of our hypotheses, we will employ a mixed-effects hierarchical logistic regression model to estimate the adjusted marginal effect over time of each intervention on the primary outcome using. Fixed effects will include intervention assignment, time period dummy variables (the baseline prescribing rate for each clinician, the intervention and intervention months 0-6, 7-12, and 13-18), and time period interacted with intervention assignment. Providers and randomization unit (clinic) will be included as random effects. To isolate the effect of each individual intervention (Suggested Alternatives, Accountable Justification, or Peer Comparison) on the primary outcome, controlling for any co-occurring interventions under the factorial design.

To assess diagnostic drift, we will use the same analytic model as for the primary outcome, but with the percentage of *all* ARIs that is coded as antibiotic-appropriate in each study arm as the dependent variable (a secondary outcome).

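### The stated random effects (provider and clinic) leave clinic-by-period variation out of the standard error of the intervention-by-period effect, so type I error exceeds 5% to the extent that clinics drift differently over time

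*Protocol*

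**What the plan says.** Protocol 9.1 (Hypotheses) sets the primary hypothesis in an "intent-to-treat difference-in-differences framework using a mixed-effects logistic regression model" and continues: "Fixed effects will include the effects of interventions over time (i.e., interactions between randomization assignment and time". Its random part is: "Providers and randomization unit (clinic) will be modeled as random effects".

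Protocol 9.5 repeats the model. The fixed effects are assignment, period dummies (baseline, then intervention months 0-6, 7-12 and 13-18) and "time period interacted with intervention assignment". The random part is: "Providers and randomization unit (clinic) will be included as random effects". The diagnostic-drift analysis is to use the same model.

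The Précis fixes the contrast: "we will compare a 6-month baseline period to an 18-month intervention period". Clinics are the unit of randomisation (3, 6.2.2, 9.2.1).

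Section 9.2 plans with one intra-clinic correlation of 0.05, a 50% baseline rate, 49 sites and 282 clinicians. It says "We assumed Type I alpha is equal to 0.05" and then calls it one-sided. No section names a clinic-by-period term, a random slope, a robust variance or a small-sample correction, and none gives a figure for how stable clinic effects are over time.

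**The concern.** Assignment is by clinic, and the effect of interest is a change between periods. The error term that matches is therefore the variation between clinics in their change, with 49 independent units.

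A constant clinic intercept drops out of each clinic's change. Given that intercept and the provider's, the model treats all visits in a clinic-period as independent. If one clinic's prescribing moves for its own reasons, the model counts that movement as visit noise, which shrinks as visits accumulate. The true uncertainty does not shrink with it.

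The protocol itself gives reasons to expect such movement. Section 9.1 (Design) notes that outside quality initiatives may run at the same time. Section 5.3 audits for shifts in diagnostic coding. Influenza is in the primary outcome, and a 6-month baseline is set against 18 months. Period dummies absorb what is common to all clinics, but not what differs between them.

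At stake are the p-values and confidence intervals of all three intervention effects and of the diagnostic-drift analysis.

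**Working it through.** **Inputs from Protocol 9.2:** ICC 0.05; baseline rate 50%; 49 clinics; 376 x 0.75 = 282 providers, so 282/49 = 5.755 per clinic; a minimum of 16 antibiotic-inappropriate visits per provider over the study; 15 ARI visits per month for a full-time provider. **From 9.5:** one 6-month baseline and three 6-month intervention periods.

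**Assumed, because the documents give no figure:** clinic autocorrelation (CAC, the share of clinic variance that is constant over time), shown at 1.0, 0.9 and 0.8; and 5 eligible visits per provider-month as a middle volume.

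**Formula.** Visit variance at a 50% rate is 0.25. Clinic variance is 0.05 x 0.25 = 0.0125, which leaves 0.2375 within clinics. Let m be a clinic's baseline visits, so 3m fall in the 18 months. For one clinic's change from baseline to the average of the three intervention periods:

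- variance the stated model sees: 0.2375 (1/m + 1/(3m)) = (4/3) x 0.2375/m
- variance it omits: 0.0125 (1 - CAC)(1 + 1/3) = (4/3) x 0.0125 (1 - CAC)

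The true standard error exceeds the model's by a factor R, where R² = 1 + m (1 - CAC) x 0.0125/0.2375 = 1 + m (1 - CAC)/19. A single 6-month period against baseline gives the same R, since 4/3 becomes 2 in both lines. Actual two-sided error is P(|Z| > 1.96/R).

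**The plan's own 5%.** At CAC 1.0, R = 1 and the error is 5.0% at any volume. The nominal level is reproduced only if clinic effects are constant.

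**Baseline visits per clinic, m.** Minimum volume: 4,504/49 = 92 visits per clinic, split 6:18 as 23 and 69, so m = 23. At 5 per month: 5 x 6 x 5.755 = 172.7. At 15 per month: 15 x 6 x 5.755 = 518.0.

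| Volume | CAC | R² | R | Two-sided error |
|---|---|---|---|---|
| 16 per provider in total | 0.9 | 1 + 2.3/19 = 1.121 | 1.06 | 6.4% |
| 16 per provider in total | 0.8 | 1 + 4.6/19 = 1.242 | 1.11 | 7.9% |
| 5 per month | 0.9 | 1 + 17.27/19 = 1.909 | 1.38 | 15.6% |
| 5 per month | 0.8 | 1 + 34.54/19 = 2.818 | 1.68 | 24.3% |
| 15 per month | 0.9 | 1 + 51.8/19 = 3.726 | 1.93 | 31.0% |
| 15 per month | 0.8 | 1 + 103.6/19 = 6.453 | 2.54 | 44.0% |

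**Scale of the ICC.** If 0.05 is read on the logit scale, clinic variance is (π²/3) x 0.05/0.95 = 0.173. On the probability scale at 50% this is 0.173/16 = 0.0108. The ratio becomes 0.0108/0.2392 = 1/22.1 in place of 1/19. The error is then 6.2-7.5%, 14-22% and 28-41% for the three volumes.

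**Simulation under no effect.** With 49 clinics in the 2x2x2 layout and intercept-only variance, two-sided rejection was about 5% without drift. With CAC 0.9 to 0.8 it was about 7-8% at 1 visit per provider-month, 13-21% at 5 and 28-39% at 15. A full logistic mixed model with clinic and provider intercepts gave 12.8% and 19.7% at 5 per month (Monte Carlo error about 1 point). One-sided, it gave 10.7% and 13.7% at 5 per month, and 6.5% and 6.0% at 1 per month. A clinic-level analysis of change held 4.5-5.7% in all cells, with and without drift.

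The ranges in the verdict use the simulated figures at 5 and 15 visits per month. The 6-9% near the minimum volume spans the table and the variant that treats the 18 months as one period (7.1% and 9.3%).

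The visit total in 9.2 does not follow from its stated inputs: 627 per level, one-sided, times 1 + 0.05 x 90.9 is 3,477, not 2,252. That is a separate matter; only the volume is used here.

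**The case against.** **The text says random effects, not intercepts, and does not say that these are the only ones.** True. A reader might infer that the protocol rules out a clinic-by-period term. It does not, and an analysis plan not shown could add one or a robust variance. But this is more than a detail left open. The protocol states the random part twice, for an interaction under clinic randomisation, and an analyst who follows it in the usual way gets the short standard error.

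**Baseline might enter as a covariate.** Section 9.5 lists each clinician's baseline rate within its period terms, and 4.1 and 9.1 limit the outcome denominator to the intervention period. Under that reading the clinic intercept would not cancel from the average effect. The Précis and 9.1 favour difference-in-differences, so this is the less likely reading, but the text should settle it.

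**The excess is conditional.** This stands. A reader might infer that the trial's false-positive rate does exceed 5%. The documents give no clinic-by-period variance, and without drift the rate is 5%.

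**The large figures depend on volume.** This stands. At the plan's minimum the excess is modest; the mixed-model run at 1 visit per month is hardly distinguishable from 5%. It is tempting to multiply 15 x 18 x 282 = 76,140 and call these eligible visits. But 15 is an ARI rate for full-time providers, before the diagnosis restriction and the exclusions. It is also tempting to give the 18 months a single clinic effect, which yields 39-52% at 15 per month. Section 9.5 has three 6-month periods, and averaging them lowers the figure.

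**The mixed-model remedy was not simulated.** True. Only the clinic-level analysis of change was shown to hold its level. A clinic-by-period random effect and cluster-robust standard errors are different methods, and their results need not agree.

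**Conclusion.** The point holds in conditional form. Read as intercepts, the random effects stated in 9.1 and 9.5 omit clinic-by-period variation from the standard error of the intervention-by-period effect. Type I error then exceeds 5% to the extent that clinics change differently over time, and the excess grows with visits per clinic.

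With ICC 0.05, 49 clinics, 282 providers and an assumed clinic autocorrelation of 0.9 to 0.8, two-sided error is about:

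- 6-9% near 16 visits per provider in total
- 13-21% at an assumed 5 eligible visits per provider-month
- 28-39% at 15 per month, an upper case
- 5% at any volume without drift

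The mechanism and the direction are firm. The size is not, because autocorrelation and eligible volume are assumptions. The protocol should be changed because it states this method for its primary test and the correction costs little.

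**What to change.** In 9.1 and 9.5, base inference for the intervention-by-period effects on between-clinic variation in change. Either add a clinic-by-period random effect to the provider and clinic effects, or use clinic-level cluster-robust standard errors. In either case, apply a small-sample correction for 49 clinics. Choose one in advance and check its type I error by simulation at the expected volume, since neither has yet been tested here. Name the clinic-level analysis of change as the supporting check; it held about 5% with and without drift.

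In the same edit, say whether baseline visits are observations in the model or a covariate, and whether the model test is one- or two-sided. Carry the change to the diagnostic-drift analysis.

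Cost: analysis wording only, with no change to data collection, randomisation or visits. Confidence intervals will be wider when clinic effects drift. In the table above, the standard error grows by a factor of 1.06-1.11 at the minimum volume and 1.38-1.68 at 5 visits per month.

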## 10. **DATA COLLECTION AND QUALITY ASSURANCE**

### 10.1 Data Collection Forms

Two types of data will be collected – data from electronic medical and billing records and data from self-administered online surveys at the beginning and end of the study.

### 10.2 Data Management

Each of the participating sites will create an extract from their Electronic Medical or Billing Records of the Data Elements for all patients with an upper respiratory infection. These records will be transferred to the coordinating center on a weekly basis.

The CC has created programs and quality control queries for transforming all of the data into a standard model (Observational Medical Outcomes Partnership Common Data Model, version 3).

The data collection forms will be online surveys. Each of the electronic data systems, Epic, NextGen, and the Longitudinal Medical Record and Partners Healthcare billing system will have native data capture formats.

### **10.3 Quality Assurance**

#### **10.3.1 Training**

Staff will be trained on the permissible values present in Electronic Records, frequency of update, and expected volumes of data.

#### **10.3.2 Quality Control Committee**

The quality control committee will consist of practicing clinicians from each participating clinical organization. They will review automatically refreshing dashboards for potential deviations in coding systems and appropriate values for codes for inclusion in the outcome measures. These dashboards will be reviewed prior to each email distribution.

#### **10.3.3 Metrics**

Quality control metrics will be based on reports verifying visits with ARI ICD-9 Codes. All drugs prescribed at these visits will be categorized as “antibiotic” or “non-antibiotic”. Incorrect categorizations will be corrected and outcome computations recomputed before each email is delivered.

#### **10.3.4 Protocol Deviations**

Our task tracking system, JIRA will be used to track and document issues. Each issue will include both an assignee and a reviewer.

#### **10.3.5 Monitoring**

In addition to data quality reviews, we will also review the integrity of the interventions.

On an approximately quarterly basis, staff will visit headquarters of participating sites and verify functionality of decision support tools.

Additionally, practicing clinicians on our study team will have the ability to monitor electronic medical record interventions in their own health systems.

## **11. PARTICIPANT RIGHTS AND CONFIDENTIALITY**

### **11.1 Institutional Review Board (IRB) Review**

The study protocol and the informed consent document for all clinic sites will be reviewed and approved by the University of Southern California’s Institutional Review Board (IRB).

Individual site protocols will also be submitted for review and approval by the Massachusetts and California site local IRBs.

### **11.2 Informed Consent Forms**

An electronically signed consent form will be obtained from each participating provider. The consent form will describe the purpose of the study, the procedures to be followed, the risks and benefits of participation, and compensation for participation.

### **11.3 Participant Confidentiality**

Data will be recorded with SSL protected web sites to a data warehouse, and transferred over secure network protocol. Data will be kept in encrypted files on computers in locked offices at USC Schaeffer Center facilities. Only study investigators will have access to a list of study ID codes that will be traceable back to actual subject contact identifiers for clinicians. These codes will be kept in locked offices at USC Schaeffer Center facilities.

Identified data will only be released to providers participating in the “Peer Comparison” arm of the study. As stored, data will be de-identified with MD5 hash to link a participant number (unique to physician) to a primary outcome. The participant number is programmatically re-identified only at the moment of an automatically scheduled e-mail. Study researchers will have password protected access to coded data only.

### **11.4 Study Discontinuation**

Following each DSMB meeting, the board will make recommendations to the local IRBs as to whether the study should continue or if changes to the protocol are necessary for continuation.

## **13. PUBLICATION OF RESEARCH FINDINGS**

Publication of results from our research will follow the NIH Public Access Policy, which requires that we submit to the National Library of Medicine’s PubMed Central an electronic version of final, peer-reviewed manuscripts upon acceptance for publication, to be made publicly available no later than 12 months after the official date of publication.

## 15. SUPPLEMENTS/APPENDICES

TABLE 1. ACUTE RESPIRATORY INFECTION DIAGNOSES RELATED TO INTERVENTIONS AND OUTCOMES ASSESSMENTS

| Diagnoses                                                                                                    | ICD9-CM                                                         | Used to Trigger Decision Support |
|--------------------------------------------------------------------------------------------------------------|-----------------------------------------------------------------|----------------------------------|
| Non-Antibiotic Appropriate ARI Diagnoses (Included in Peer Comparison and Primary Outcome Assessment) |                                                                 |                                  |
| Acute nasopharyngitis (common cold)                                                                          | 460                                                             | non-specific URI                 |
| Acute laryngitis and tracheitis                                                                              | 464, 464.0, 464.00, 464.1, 464.10, 464.2, 464.20, 464.4, 464.50 | non-specific URI                 |
| Acute laryngeopharyngitis/acute upper resp infection                                                         | 465, 465.0, 465.8, 465.9                                        | non-specific URI                 |
| Acute bronchitis                                                                                             | 466, 466.0, 466.1, 466.11, 466.19                               | acute bronchitis                 |
| Bronchitis not specified as acute or chronic                                                                 | 490                                                             | acute bronchitis                 |
| Influenza                                                                                                    | 487, 487.1, 487.8                                               | influenza                        |
| Potentially Antibiotic Appropriate ARI Diagnoses (Included in Secondary Outcome Assessment)           |                                                                 |                                  |
| Acute sinusitis                                                                                              | 461.xx                                                          | acute sinusitis/rhinosinusitis   |
| Acute pharyngitis                                                                                            | 462                                                             | acute pharyngitis                |
| Other ARIs Diagnoses or Symptoms of Interest (Included in Secondary Outcome Assessment)*              |                                                                 |                                  |
| Streptococcal sore throat                                                                                    | 034.0                                                           | acute pharyngitis                |
| Cough                                                                                                        | 786.2                                                           | acute bronchitis                 |

Only additional diagnoses triggering clinical decision support are included here. Additional diagnoses included in the secondary outcomes are listed in Supplemental Appendix E.

## APPENDIX A: SURVEY AND SAMPLE EDUCATIONAL MODULE AT START OF STUDY

### Online Survey

THE ONLINE SURVEY IS INTENDED TO (1) ELICIT INFORMATION FROM PROVIDERS (2) MONITOR IF “EDUCATON” INFLUENCES RESPONSES TO QUESTIONS ABOUT TREATMENT PREFERENCES. RESPONDENTS WILL HAVE THE OPPORTUNITY TO CHANGE THEIR ‘FINAL’ ANSWERS AT ANY TIME IN THE SURVEY. WE WILL RECORD ALL ANSWERS AND LOG CLICKS ON INFORMATIONAL LINKS PROVIDED.

### Basic information about your clinical background.

1. When did you start working at [*name of clinic*]? (<1 year ago, 1-2 years ago, 3-5 years ago, 5-10 years ago, >10 years ago)
2. When did you finish your clinical training as a physician (i.e., your internship, residency, or fellowship—the one you most recently completed)? (<2 years ago, 2-5 years ago, 5-10 years ago, 10-20 years ago, >20 years ago)
3. What is your clinical specialty? (internal medicine, family practice, general practice, pediatrics, other)

### Information about the electronic health record (EHR) used at your clinic.

4. How would you rate your overall level of satisfaction with the electronic health record (EHR) used at your clinic?  
(1= Very unsatisfied , 5=Very satisfied)
5. Thinking about your workflow during an office visit with a patient, how often do you enter at least 1 diagnosis for the visit into the EHR while you are still seeing the patient?
  - a. Always
  - b. Usually
  - c. Sometimes
  - d. Rarely
  - e. Never
  - f. Not applicable: The EHR does not offer a way to enter a diagnosis (or diagnoses) that correspond to the visit.

Quality improvement efforts.

6. Within the past year, have you received any feedback—positive or negative—from your clinic about the quality of care you provide to patients (for any kind of care)?
  - a. Yes, positive feedback only
  - b. Yes, both positive and negative feedback
  - c. Yes, negative feedback only
  - d. No, did not receive any feedback at all
  - e. Unsure / Can't Remember
  
7. [If yes to previous] Based on the feedback you received, did you make any changes to the way you deliver medical care?
  - a. Yes, made 1 or more changes
  - b. No, made no changes
  - c. Unsure / Can't Remember
  
8. In the past year, did you attend any medical educational sessions? *Note: "Medical education sessions" include sessions that yielded credit towards maintenance of certification (e.g., CME) and less formal sessions that did not yield such credit.*
  - a. Yes
  - b. No
  - c. Unsure / Can't Remember
  
9. [If yes to question 8] Based on the information you received in any of these educational sessions, did you make any changes to the way you deliver medical care?
  - a. Yes, made 1 or more changes
  - b. No, made no changes
  - c. Unsure / Can't Remember
  
10. [If yes to question 8] Did any of the educational sessions you attended cover the office-based treatment of acute respiratory infections (e.g., viral URIs, pharyngitis, bronchitis)?
  - a. Yes
  - b. No
  - c. Unsure / Can't Remember

11. [If yes to question 8] Did any of the educational sessions you attended cover the office-based treatment of acute low back pain?

- a. Yes
- b. No
- c. Unsure / Can't Remember

12. Based on your general experience as a clinician, please indicate how much you agree or disagree with the following statements:

- i. Continuing education is an effective way to improve the quality of care (1 = Strongly agree, 2 = Agree, 3 = Neither Agree nor Disagree, 4 = Disagree, 5 = Strongly Disagree)
- ii. Auditing physicians' clinical performance and providing performance feedback is an effective way to improve the quality of care (1 = Strongly agree, 2 = Agree, 3 = Neither Agree nor Disagree, 4 = Disagree, 5 = Strongly Disagree)
- iii. Electronic decision support tools (e.g., "pop up" reminders in your EHR) are an effective way to improve the quality of care (1 = Strongly agree, 2 = Agree, 3 = Neither Agree nor Disagree, 4 = Disagree, 5 = Strongly Disagree)
- iv. Condition-specific, streamlined electronic order sets are an effective way to improve the quality of care (1 = Strongly agree, 2 = Agree, 3 = Neither Agree nor Disagree, 4 = Disagree, 5 = Strongly Disagree)

Your assessment of clinical guidelines.

|                                                                                                                                                                                                                  |                                                                                                                           |
|------------------------------------------------------------------------------------------------------------------------------------------------------------------------------------------------------------------|---------------------------------------------------------------------------------------------------------------------------|
| 13. Please indicate your level of knowledge about the following clinical guidelines.                                                                                                                             | [Know this guideline in detail / Know this guideline in general, but not every detail / Not familiar with this guideline] |
| Screening                                                                                                                                                                                                 |                                                                                                                           |
| Guidelines for colorectal cancer screening (USPSTF guideline:
http://www.uspreventiveservicestaskforce.org/uspstf/uspcolo.htm ) |                                                                                                                           |
| Guidelines for breast cancer screening (USPSTF guideline:
http://www.uspreventiveservicestaskforce.org/uspstf/uspbrca.htm )     |                                                                                                                           |
| Guidelines for cervical cancer screening (USPSTF guideline:
http://www.uspreventiveservicestaskforce.org/uspstf/uspccerv.htm ) |                                                                                                                           |
| Chronic disease care                                                                                                                                                                                      |                                                                                                                           |
| Guidelines for the care of diabetes mellitus (ADA guideline:
http://www.guideline.gov/content.aspx?id=15687 )                                    |                                                                                                                           |
| Guidelines for lipid and cholesterol management (ATP III guidelines:
http://circ.ahajournals.org/cgi/reprint/106/25/3143 )                  |                                                                                                                           |
| Acute care                                                                                                                                                                                                |                                                                                                                           |
| Guidelines for antibiotic use in non-specific upper respiratory infections
(CDC guidelines: http://www.annals.org/content/134/6/490.abstract ) |                                                                                                                           |
| Guidelines for imaging in acute low back pain (ACP/APS guidelines:
http://www.annals.org/content/147/7/478.full.pdf+html )                |                                                                                                                           |

**a. In the grid below, please estimate the AVERAGE time allocated to you and amount of time you feel would be needed to provide high quality care for your patients. (please check one box)**

| Visit type                                              | Time allocated | Time needed |
|---------------------------------------------------------|-----------------------|--------------------|
| i. Complete Physical/Consultation                       | _____ minutes         | _____ minutes      |
| ii. Routine Follow-up Visits                            | _____ minutes         | _____ minutes      |
| iii. Urgent Care Visits (in general)                    | _____ minutes         | _____ minutes      |
| iv. Urgent Care Visits for acute respiratory infections | _____ minutes         | _____ minutes      |

